**Fig. 2 Fig2:**
[figure not shown]
MAiBest study design

A)Analysis of determinants of patients PP usage

The trend survey at the three measurement time points (t0; t1; t2) allows for the depiction of determinants of PP usage and the expected changes in these determinants over time. The t0 survey captures the clinic-specific heterogeneity of patient-related determinants for PP use and enabling an adjustment of the trend analysis for these baseline values from t0. This facilitates the examination of trends within each clinic and allows for comparisons between the three clinics. Patients treated in the three clinics at the three measurement time points (t0; t1; t2), whether inpatient or outpatient, will receive a paper-based questionnaire with additional, optional access to a digital version. These questionnaires include items measuring patient-related determinants and, additionally, usage behavior in t1 and t2. The patient surveys are based on existing and validated scales (e.g. digital literacy [26], technology acceptance [20], or if not possible, on items developed according to methodological standards [23]. Additionally, socioeconomic and sociodemographic factors (e.g., age, gender, education, income) are recorded for later adjustment.

The sample size calculation results in a required rounded *N* = 200 patients per measurement time point per clinic (pooled total *N* = 1800). This is based on an assumed weak effect size for Cohen's D of 0.2 with 80% power and a significance level of 0.05 for a (1) two-sided independent two-sample t-test for the comparison between clinics at each measurement time point (total *N* = 393 at each time point for the comparison between two clinics, rounded *n* = 200 per clinic) and (2) for the comparison within the clinic across measurement time points in a two-sided paired t-test (required *n* = 198 per time point). The data analysis is performed using descriptive and inferential statistics, adjusting for previously collected socioeconomic and sociodemographic characteristics, conducted with the statistical software SPSS^©^.

B)Analysis of determinants of physicians PP usage

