
E)Analysis of changes in internal administrative and clinical parameters

In light of the fact that it is unclear to what extent the DOI can be applied to PP, it is unclear to what extent the hospital data collected for administrative purposes is suitable for making statements regarding potential improvements in care. To identify outcomes relevant for future research projects, an exploratory analytical approach is applied to the hospital data collected for administrative purposes from one participating clinic. If the utilization of PP leads to improvements in clinical outcomes, these improvements would be reflected in the administrative and clinical management data. For instance, parameters mentioned by Dumitrascu [10] such as the 30-day readmission rate, inpatient mortality, or 30-day mortality are analyzed. The data consist of administrative data for all outpatient and inpatient patients within a month at the three measurement points (t0; t1; t2). Data analysis involves descriptive and inferential statistics to compare the means of the examined parameters regarding potential differences at the three measurement points. The results provide initial indications of whether the parameters investigated here are suitable for assessing potential impacts of the PP on clinical outcomes in further research projects.

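### Part E compares means at three single months in one clinic and names no separation by setting and no case-mix adjustment, so a change in patient mix is confounded with the portal

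*Protocol article*

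**What the plan says.** The plan for part E is in the protocol article, Methods / design, E) Analysis of changes in internal administrative and clinical parameters.

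- **Site and status:** "an exploratory analytical approach is applied to the hospital data collected for administrative purposes from one participating clinic".
- **Data:** "administrative data for all outpatient and inpatient patients within a month", at each of the three measurement points.
- **Parameters:** examples "such as the 30-day readmission rate, inpatient mortality, or 30-day mortality are analyzed".
- **Method:** descriptive and inferential statistics to "compare the means of the examined parameters regarding potential differences at the three measurement points". No covariate, stratum or standardisation is named.
- **Use of the result:** "The results provide initial indications of whether the parameters investigated here are suitable for assessing potential impacts of the PP on clinical outcomes" in later projects. The section also states the premise: "If the utilization of PP leads to improvements in clinical outcomes, these improvements would be reflected in the administrative and clinical management data".

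The matching sentence in part A continues with "adjusting for previously collected socioeconomic and sociodemographic characteristics", and part B has an equivalent clause. Methods / design places t0 at 2 months before implementation and t1 and t2 at 6 and 12 months after it.

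**The concern.** Mortality and readmission usually differ by setting, by age and by planned or acute admission. A mean over patients of different risk changes when their shares change, even if the risk within every group stays the same. Part E has one clinic, three single months and no comparison clinic, so nothing in the stated design separates such a change from the portal.

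The article itself treats setting as important. Hypothesis A4 in Table 1 expects use of the digital anamnesis to differ between planned inpatients and acute outpatients, and the Theory section asks whether determinants depend on the outpatient or inpatient context.

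At stake is the one purpose of part E, the judgement of which parameters suit later research. A parameter may look responsive because the mix moved, or a real change may be masked. Later projects would inherit that choice.

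**Working it through.** Part E states no rate, sample size or effect, so there is no figure of the plan to reproduce. The check has three steps.

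**1. Timing (from Methods / design).** t0 to t1: 6 − (−2) = 8 months. t0 to t2: 12 − (−2) = 14 months. Neither t1 nor t2 falls in the same calendar month as t0.

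**2. Effect of mix alone.** Let w be the share of the higher-risk group, pH and pL the two risks, and m = w·pH + (1 − w)·pL the overall rate. With no portal effect, a shift d in w changes the rate in relative terms by d·(pH − pL)/m. All rates and shares below are assumptions; d is 5 points.

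| Parameter and strata | pH, pL | Starting share w | Relative change |
|---|---|---|---|
| 30-day mortality, inpatient/outpatient | 3%, 0.3% | 20%, 40%, 60% | 16.1%, 9.8%, 7.0% |
| 30-day mortality, inpatient/outpatient | 2%, 0.5% | 20%, 40%, 60% | 9.4%, 6.8%, 5.4% |
| Inpatient mortality, higher/lower risk | 6%, 1% | 30%, 50% | 10.0%, 7.1% |
| Inpatient mortality, higher/lower risk | 4%, 2% | 30%, 50% | 3.8%, 3.3% |
| Readmission, two risk groups | 12%, 3% | 20%, 40%, 60% | 9.4%, 6.8%, 5.4% |
| Readmission, two risk groups | 10%, 6% | 20%, 40%, 60% | 2.9%, 2.6%, 2.4% |

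First row at w = 40%: m = 0.4 × 3% + 0.6 × 0.3% = 1.38%, and 0.05 × 2.7% / 1.38% = 9.8%. The whole range is about 2% to 16%.

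The inpatient share matters mainly for 30-day mortality. Inpatient mortality, and normally readmission, are counted among admitted patients, so for them the relevant shift is in age or acute/planned mix within inpatients.

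**3. Comparison with a portal effect.** If users and non-users have the same baseline risk, the change in the clinic rate is uptake × relative effect in users. Assumed values: 0.30 × 10% = 3%; 0.50 × 20% = 10%. The mix shift that equals a relative effect r is r·m/(pH − pL). At w = 40% and r = 10%:

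- 3% and 0.3%: 0.10 × 1.38 / 2.7 = 5.1 points.
- 10% and 6%: 0.10 × 7.6 / 4 = 19.0 points.

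So a plausible-looking mix shift can match a modest portal effect when the strata differ strongly, and falls well short when they do not.

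**Effect on a test.** With risks of 12% and 3%, a 10-point shift (40% to 50%) alone is rejected at two-sided 0.05 with probability 0.08, 0.12 and 0.20 for 500, 1000 and 2000 patients per month. A 5-point shift gives about 0.08 at 2000. The main harm is therefore a biased estimate, more than frequent false significance.

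**The case against.** The strongest reply is that silence is being read as a choice. A reader might infer that the plan prescribes a crude mean over one pool of outpatients and inpatients. The text does not say that: it uses none of those terms, inferential statistics can include covariates, and an article may leave them to the full plan. Describing the data extract as covering both settings also does not fix one common denominator.

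This limits the point but does not remove it. The article does report adjustment for A and B, and where that clause stands in their analysis sentences, part E puts the comparison of means. The covariates in A and B come from questionnaires, and no linkage to the administrative data is described, so that adjustment cannot be assumed to carry over.

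A second reply is that E1 is exploratory and asks only what changes occur, which observed means can answer. That is fair for description and lowers the priority. It does not cover the further step of judging whether a parameter is suitable for detecting portal effects.

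A third reply is that a rich regression may not be feasible. Assuming 300 inpatients a month and 3% mortality, three months give 300 × 3 × 0.03 = 27 deaths. This stands, and the fix is scaled accordingly.

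**Conclusion.** The concern holds in limited form. As written, part E names no means of separating a change in patient mix from a portal effect, in a design with three single months and no comparison clinic. Under assumed rates, a 5-point shift moves a parameter by roughly 2% to 16%, about as much as a modest portal effect of 3% to 10% on the clinic rate.

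A reader might go further and infer that mix shifts outweigh any plausible portal effect. The document does not support that. It gives no rate, inpatient share, uptake or expected effect, and nothing shows that the mix in this clinic moves by 5 points. With risks of 10% and 6%, a 5-point shift moves the rate by under 3%, and against a 20% change in the clinic rate a mix shift would seldom compete.

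Priority is modest, since part E is exploratory and claims only initial indications.

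**What to change.** In Methods / design, E), replace the comparison of means by the following:

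- Compare each parameter between time points separately for inpatients and outpatients, with its denominator defined. Count readmission and inpatient mortality among admitted patients only.
- Beside each crude value, report a time-point contrast adjusted for, or standardised to, a few routine fields such as age, sex and planned/acute admission.
- Add diagnosis group only where event numbers allow. For rare deaths, use for example penalised logistic regression.

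Separating the settings removes the part of a change due to the inpatient share. It leaves mix within inpatients (3.3% to 10.0% for a 5-point shift in the mortality rows above), which is why the second step is needed.

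The cost is a little more analysis and no new patients. It depends on these fields being in the extract, which the article does not describe. Intervals for rare events will be wider, and unmeasured severity stays uncontrolled, so a remaining change still cannot be credited to the portal with confidence.

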## Discussion

The reasons for potential usage barriers are diverse and can be caused both by a suboptimal implementation process and by users themselves [8]. For the present research project, it is assumed that implementation-related factors can be largely neglected. This assumption can be made because the participating hospital possesses an institutionally anchored and experienced implementation team (Department of Digital Clinical Systems) for implementing digital innovations. In recent years, various digital innovations have been successfully implemented, including the requirements for the national telematics infrastructure and the electronic health record, the introduction of a digital fever chart, and the implementation of a patient data management system in the intensive care unit. For the planned implementation of the PP, both, patient-centered and provider-centered implementation and communication strategies were developed, for which the hospital was awarded with the "German CHANGE Award 2022" [14]. Against this background, the assumption that existing barriers do not arise from the implementation process, but are actually to be found in the respective users, can be regarded as legitimate. The results can therefore be assumed relevant for all German hospitals, regardless of their implementation strategies. Another point to emphasize with regard to the relevance of the results is the projects participatory approach. The whole project, from the research questions to the use case of DAC and the study design, has been collaboratively developed with the clinical team of the Department of Digital Clinical Systems. Through this close collaboration between science and practice, the expected results have particular utility for other hospitals during the implementation of PPs.

However, the academic teaching hospital underlying the research project might distinguish itself from other hospitals by a particularly pronounced innovation climate. It is possible that this innovation climate may be less pronounced in smaller hospitals, potentially limiting the translatability of the results. Nevertheless, the guiding theory of DOI is based on a universal claim. If the theory-driven hypotheses can be accepted and research questions are answered, a possible generalizability of the results may be derived, suggesting that those determinants and barriers proving to be time-constant could be identified across different hospitals, irrespective of their innovation climate.

## Conclusion

The anticipated results will reveal (A) patient-related and (B) physician-related determinants, influencing PP usage. Additionally, (C) barriers to PP usage and reasons for non-usage will be identified. In exploratory approaches (D) the actual PP usage on the level of documentation and (E) potential changes in administratively collected data will be examined. Given that hospitals nationwide are mandated to implement PPs and the questions pursued in this study remain unanswered at the national level, the practical significance of the findings is substantial. The results, along with derived "Dos and Don'ts" for practical implementation, will support other hospitals when implementing their PPs. Furthermore, the insights can serve as guidance for software developers in aligning the development of PPs with user requirements.

## Data Availability

Not applicable.

## Abbreviations

PP: Patient Portal
DAC: Digital Anamnesis Collection
DOI: Diffusion of Innovation
